## Abstract

**Background:**

Molecular point-of-care testing (POCT) used in primary care can inform whether a patient presenting with an acute respiratory infection has influenza. A confirmed clinical diagnosis, particularly early in the disease, could inform better antimicrobial stewardship. Social distancing and lockdowns during the COVID-19 pandemic have disturbed previous patterns of influenza infections in 2021. However, data from samples taken in the last quarter of 2022 suggest that influenza represents 36% of sentinel network positive virology, compared with 24% for respiratory syncytial virus. Problems with integration into the clinical workflow is a known barrier to incorporating technology into routine care.

**Objective:**

This study aims to report the impact of POCT for influenza on antimicrobial prescribing in primary care. We will additionally describe severe outcomes of infection (hospitalization and mortality) and how POCT is integrated into primary care workflows.

**Methods:**

The impact of POCT for influenza on antimicrobial stewardship (PIAMS) in UK primary care is an observational study being conducted between December 2022 and May 2023 and involving 10 practices that contribute data to the English sentinel network. Up to 1000 people who present to participating practices with respiratory symptoms will be swabbed and tested with a rapid molecular POCT analyzer in the practice. Antimicrobial prescribing and other study outcomes will be collected by linking information from the POCT analyzer with data from the patient’s computerized medical record. We will collect data on how POCT is incorporated into practice using data flow diagrams, unified modeling language use case diagrams, and Business Process Modeling Notation.

**Results:**

We will present the crude and adjusted odds of antimicrobial prescribing (all antibiotics and antivirals) given a POCT diagnosis of influenza, stratifying by whether individuals have a respiratory or other relevant diagnosis (eg, bronchiectasis). We will also present the rates of hospital referrals and deaths related to influenza infection in PIAMS study practices compared with a set of matched practices in the sentinel network and the rest of the network. We will describe any difference in implementation models in terms of staff involved and workflow.

**Conclusions:**

This study will generate data on the impact of POCT testing for influenza in primary care as well as help to inform about the feasibility of incorporating POCT into primary care workflows. It will inform the design of future larger studies about the effectiveness and cost-effectiveness of POCT to improve antimicrobial stewardship and any impact on severe outcomes.

**International Registered Report Identifier (IRRID):**

DERR1-10.2196/46938

## Introduction

### Rapid Testing for Influenza in a Postpandemic Health Service

Measures to limit SARS-CoV-2 transmission during the COVID-19 pandemic coincided with a marked decrease in infections caused by other respiratory viruses [1,2].

After the lifting of COVID-19 containment measures, the robust return of influenza, seasonal coronaviruses, parainfluenza virus, and respiratory syncytial virus (RSV) was observed in many countries including the United Kingdom [3].

Figure 1 and Table 1 show data from the English national sentinel surveillance network as of the end of November 2022. Influenza and RSV were the main circulating respiratory viruses, with SARS-CoV-2 making up only 12.4% (15/121) of the total number of laboratory-confirmed cases.

**Figure 1 figure1:**
[figure not shown]
Swab positivity by week in the English national sentinel surveillance network from March 2022 to January 2023 [4]. hMPV: human metapneumovirus; RSV: respiratory syncytial virus.

In the context of a postpandemic health care service where there are high levels of circulating influenza, accurate, rapid molecular diagnostic test platforms have the potential to (1) improve clinical decision-making regarding the use of antibiotics and antivirals, (2) improve patient outcomes due to the early appropriate use of antivirals, and (3) provide better information to inform sentinel surveillance and clinical research including studies of vaccine effectiveness and real-world trials [5,6].

Specifically, for patients with influenza infection, early diagnosis and administration of antivirals may improve clinical outcomes [7,8]. They may also limit symptom duration and spread to household contacts, and newer antivirals for influenza, such as baloxavir, have been shown to improve the time to resolution of symptoms and reduce complications in high-risk patients [9].

Currently, only a small proportion of patients with respiratory tract infections (RTIs) undergoes diagnostic microbiological testing before receiving treatments in primary care [10], and there is evidence of widespread variations in antimicrobial prescribing practices [11]. This is important, as prescribing in primary care accounts for about 8% of National Health Service (NHS) expenditure, which is equivalent to over £9 billion (US $11.1 billion) per year, with just over £220 million (US $271.5 million) being spent on antimicrobials [12]. Inappropriate prescribing of antimicrobials and unwarranted variation in prescribing can contribute to increase of antimicrobial-resistant strains and patient adverse events in the short and long term [13].

We have previously shown that, in a prepandemic context, it is feasible to undertake point-of-care testing (POCT) for influenza in primary care in the England, with promising impacts on antimicrobial use and estimates of influenza vaccine effectiveness that are comparable with published data [14-16]. However, its impact on more severe outcomes such as hospitalization and mortality following infection has not been reported.

Recent work on in-pandemic prescribing of azithromycin and doxycycline for RTIs across the sentinel network has shown scope for measures to improve antibiotic stewardship in primary care [17].

With the ending of widespread national testing for SARS-CoV-2 and other RTIs in the United Kingdom in March 2022 [18] and with high levels of circulating influenza in a post-COVID-19 health service during the autumn 2022 compared with 2021, there is a need to revisit questions about the feasibility of implementing rapid diagnosis of influenza during the expected peak of viral circulation this winter (2022-2023) season and its impact on clinical management in terms of improved antimicrobial stewardship and severe outcomes (hospitalization and mortality).

**Table 1 table1:** Swab positivity by week in the English national sentinel surveillance network between September 2022 and November 2022 (n=818).

Week commencing	Swab positivity					
	Adenovirus (n=54)	hMPV^a^ (n=85)	Influenza (n=215)	Other coronaviruses (n=13)	RSV^b^ (n=255)	SARS-CoV-2 (n=196)
9/26/2022 (n=26), n (%)	0 (0)	0 (0)	0 (0)	0 (0)	11 (42.3)	15 (57.7)
10/3/2022 (n=54), n (%)	0 (0)	1 (1.9)	20 (37)	0 (0)	6 (11.1)	27 (50)
10/10/2022 (n=52), n (%)	0 (0)	2 (3.8)	14 (26.9)	1 (1.9)	6 (11.5)	29 (55.8)
10/17/2022 (n=70), n (%)	0 (0)	6 (8.6)	19 (27.1	2 (2.9)	17 (24.3	26 (37.1)
10/24/2022 (n=82), n (%)	0 (0)	6 (7.3)	28 (34.1	0 (0)	30 (36.6	18 (22)
10/31/2022 (n=94), n (%)	9 (9.6)	9 (9.6)	31 (33)	1 (1.1)	24 (25.5	20 (21.3)
11/7/2022 (n=95), n (%)	12 (12.6)	11 (11.6)	16 (16.8)	4 (4.2)	35 (36.8)	17 (17.9)
11/14/2022 (n=122), n (%)	6 (4.9)	18 (14.8)	34 (27.9)	2 (1.6)	42 (34.4)	20 (16.4)
11/21/2022 (n=102), n (%)	12 (11.8)	14 (13.7)	27 (26.5)	0 (0)	40 (39.2)	9 (8.8)
11/28/2022 (n=121), n (%)	15 (12.4)	18 (14.9)	26 (21.5)	3 (2.5)	44 (36.4)	15 (12.4)

^a^hMPV: human metapneumovirus.

^b^RSV: respiratory syncytial virus.

### Objectives

This study aims to report the impact of POCT for influenza on antimicrobial prescribing in primary care. We will additionally describe severe outcomes postinfection (hospitalization and mortality) and how POCT is integrated into primary care workflows.

## Methods

### Study Setting and Population

The impact of POCT for influenza on antimicrobial stewardship (PIAMS) study will take place between December 2022 and May 2023, during the influenza season as defined by the UK Health Security Agency (UKHSA). It is nested within the English national sentinel network managed by the Oxford-Royal College of General Practitioners (RCGP) Research and Surveillance Centre (RSC) at the Nuffield Department of Primary Care, University of Oxford. This network of over 1800 primary care practices is the primary infectious disease surveillance network for England, which is generally representative of the English population [19]. It has been providing weekly infection data for over 50 years that are used to monitor trends in infectious disease and investigate real-world vaccine and treatment effectiveness [20].

All practices that contribute data to the English national sentinel network will be invited to participate in the PIAMS study, and 10 practices will be selected to take part in the PIAMS study. We will prioritize practices within the network with capacity to undertake influenza POCT and who had previously been involved in SARS-CoV-2 POCT through the RAPTOR-C19 study [21]. Those practices that have a history of less than 80% complete data returns during the previous winter season will be excluded.

Each participant practice will receive training about the study, including hands-on training on how to administer a swab test and how to use the POCT analyzers.

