Antimicrobial prescribing and other study outcomes for those who have been swabbed will be obtained by linking information from the cobas Liat analyzer with data from the patient’s computerized medical record in primary care. We will demonstrate the feasibility of reporting antimicrobial stewardship and severe outcomes postinfection. Severe outcomes postinfection such as hospitalization and mortality will be obtained by linking the patient’s primary care computerized medical record to secondary care records at the national level including hospitalization and mortality data. A recent study used a linked cohort to study severe outcomes from COVID-19 infection [25].

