To answer our secondary objective, we will select a matched set of practices from the rest of the English national sentinel network based on practice size, average age of registered patients, proportion of registered female patients, and number of GPs employed during the study.

The rates of hospital referrals and deaths related to influenza infection within 30 days of diagnosis will be compared between PIAMS study practices and the rest of the network using the ANOVA test.

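### The 80% data-return rule screens PIAMS practices but not their comparators, which risks unequal capture of influenza diagnoses and possibly referrals in the severe-outcome comparison

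*Protocol article*

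**What the plan says.** In Study Setting and Population, the Protocol article says that "10 practices will be selected to take part in the PIAMS study". The same paragraph sets the completeness bar: "Those practices that have a history of less than 80% complete data returns during the previous winter season will be excluded".

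For the secondary objective, Statistical Methods selects a matched set of network practices "based on practice size, average age of registered patients, proportion of registered female patients, and number of GPs employed during the study". None of these four criteria concerns data completeness. Rates of hospital referral and influenza-related death within 30 days of diagnosis "will be compared between PIAMS study practices and the rest of the network using the ANOVA test", and no restriction is placed on that network. The Results paragraph of the Abstract names both comparators: PIAMS practices are to be "compared with a set of matched practices in the sentinel network and the rest of the network".

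On sources, the section on face-to-face recruitment gives the route for severe outcomes: "linking the patient’s primary care computerized medical record to secondary care records at the national level including hospitalization and mortality data". The article does not say whether the hospital referrals in Statistical Methods are GP-recorded referrals or linked admissions. It does not give the denominator of the rates either.

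**The concern.** One side of the comparison is filtered on the completeness of its primary care data and the other is not. The rest of the network includes, by definition, any practice barred from PIAMS for poor returns. The matched set may include such practices, because nothing in the matching keeps them out.

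The filter bears on data that the outcome needs. The 30-day window starts at an influenza diagnosis, which is a primary care record. A referral is also a primary care record if it is taken from the GP system. Where returns are missing, diagnoses and referrals may go uncounted while the registered population stays in place. A rate per registered patient would then be understated in the comparator, and PIAMS practices would seem to have more severe outcomes even if the true rates were equal. A real benefit of POCT could be masked, or an apparent harm attributed to it.

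**Working it through.** No stated figure in the article bears on this point, so there is nothing to reproduce. The check has three parts.

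**1. Scope of the rule.** The completeness bar appears once, in the paragraph that selects the PIAMS practices. The matching list has four items (size, mean age, proportion female, number of GPs), and the rest of the network has no entry condition. As written, the rule does not reach either comparator.

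**2. Which outcomes are exposed.**
- Index diagnosis: a primary care record, so exposed.
- Referrals: exposed if taken from GP records. The source is not stated.
- Deaths and admissions from national linkage: not lost through poor returns, unless the diagnosis that opens the window is missing.

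**3. Possible size, with rates per registered patient and a true ratio of 1.** The article gives none of these inputs, so all are assumptions:
- *c*: completeness in PIAMS practices and in comparator practices that meet the rule (80%, 90% or 100%)
- *s*: share of comparator practices below 80% (0 to 40%)
- *l*: completeness in those low-return practices (50% or 70%)
- events are lost in proportion to missing returns

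Comparator completeness = (1 − *s*)·*c* + *s*·*l*. Spurious ratio = *c* / [(1 − *s*)·*c* + *s*·*l*].

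| *c* | *l* | *s* = 10% | *s* = 20% | *s* = 40% |
|---|---|---|---|---|
| 80% | 70% | 1.013 | 1.026 | 1.053 |
| 80% | 50% | 1.039 | 1.081 | 1.176 |
| 90% | 70% | 1.023 | 1.047 | 1.098 |
| 90% | 50% | 1.047 | 1.098 | 1.216 |
| 100% | 70% | 1.031 | 1.064 | 1.136 |
| 100% | 50% | 1.053 | 1.111 | 1.250 |

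Example: *c* = 0.90, *l* = 0.50, *s* = 0.20 gives 0.80 × 0.90 + 0.20 × 0.50 = 0.82, and 0.90 / 0.82 = 1.098. With *s* = 0 the ratio is 1.00 in every row.

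**With rates per diagnosed case instead.** If a missing return removes a diagnosis together with its event, a captured fraction *k* gives (*k* × events) / (*k* × diagnoses) = events / diagnoses, and the loss cancels. It fails to cancel only where the diagnosis is kept and its referral is lost.

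**The case against.** Much of the case on the other side is sound.

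- **No completeness data.** The article gives no completeness for comparator practices and no share below 80%. The rule looks at the previous winter, not the study season. A reader might infer that the comparators are in fact less complete and that the comparison is biased; the article supports neither statement. The rule still has a purpose only if last winter's returns are expected to predict this season's, and that reasoning applies equally to comparators.
- **National linkage.** This largely protects deaths and admissions. What remains exposed is the index diagnosis, and referrals if they are GP-recorded.
- **Meaning of complete returns.** The term is undefined, so the step from missing returns to an equal share of missing events is an assumption.
- **Denominator.** Because it is not stated, a bias against PIAMS follows only on the per-registered-patient reading.
- **Matched set.** It might seem that both comparators must contain the low-return practices. That holds only for the rest of the network. A matched subset need not contain any.
- **Left to the analysis plan.** Data filters are often set there, and this is a condensed article. But the article itself states both the PIAMS filter and the comparator criteria, and the two differ.
- **Standing of the outcome.** Severe outcomes are secondary and largely descriptive, and the article acknowledges the nonrandomized design. POCT itself, used only in PIAMS practices, may be the larger source of unequal influenza ascertainment.

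These points limit the size and certainty of the problem. They do not remove the mismatch in eligibility.

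**Conclusion.** The point holds as a risk of differential ascertainment. The plan applies a completeness criterion to PIAMS practices and to neither comparator. It could distort the comparison through missing influenza diagnoses and, depending on their source, missing referrals, mainly in the rest of the network.

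The size is unknown. On the assumed inputs above and a per-registered-patient rate, the spurious ratio against PIAMS lies between 1.00 and 1.25. It is about 1.01 to 1.05 if 10% of comparator practices fail the rule. The upper end needs 40% of comparator practices to fail with half their data missing, and nothing in the article suggests that. This is a modest weakness in a secondary comparison, worth correcting because the correction is cheap.

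**What to change.** In Statistical Methods, under the secondary objective, restrict both the matched set and the rest-of-network comparator to practices with at least 80% complete data returns in the previous winter season, the same criterion used for PIAMS practices. Keep the unrestricted network as a sensitivity comparison. It would help to report completeness by group in the same place, and to state the denominator of the rates and whether referrals come from GP records or linked admissions.

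The cost is one sentence and a somewhat smaller comparator. With over 1800 practices in the network and 10 in PIAMS, even a 40% failure rate would leave roughly 0.6 × 1790 ≈ 1074 practices, so the loss of precision is negligible. All network practices are invited, so the completeness measure is probably available for them. The article does not say that all are screened on it, and the sponsor should confirm this.

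If completeness is equal once the rule is applied, the spurious ratio from this source returns to 1.00. The difference in influenza ascertainment caused by testing only in PIAMS practices would remain and needs separate handling.

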### Case Definition of Eligible Patients

All patients registered within the PIAMS study practice who do not have an opt-out code on their medical record and are showing symptoms of influenza-like illness (ILI), acute respiratory illness (ARI), or fever of higher than 37.5 °C will be eligible for the study if they consent to participate. We will use the European Centre for Disease Prevention and Control case definitions of ILI and ARI for this study. We will use the following exclusion criteria: (1) patient has an opt-out code on their medical record or (2) no informed consent.

### Face-to-face Recruitment of Eligible Patients and Point-of-care Testing for Influenza

We will undertake opportunistic swab sampling for this study, with potential participants being identified from those registered patients who present to the study practice with respiratory symptoms described in the case definition. No screening nor eligibility assessment will be undertaken. Blinding of participants and researchers will not be undertaken.

Eligible patients or their parent or legal guardian will be approached by a practice general practitioner (GP) or research nurse to explain the study and ask for consent to take part when they present for a face-to-face consultation at the practice.

After obtaining consent, a nasopharyngeal swab will be taken by a suitably qualified and experienced GP or research nurse. For those who do not attend the practice in person, a self-test kit will be sent to their home.

The cobas Liat POCT analyzer, manufactured by Roche Diagnostics International, will be used for this study [22]. This POCT analyzer is an automated multiplex polymerase chain reaction system, with previous studies demonstrating excellent performance comparable with gold standard laboratory assays, with sensitivity and specificity in the region of 100% and 97.1%-100%, respectively, for influenza A and 97.8%-100% and 99.5%-99.7%, respectively, for influenza B when fresh, prospectively collected samples are tested [23,24]. It has CE-marking in the European Union. In the United States, it is Food and Drug Administration–cleared, and it is also Clinical Laboratory Improvement Amendments–waived for use for rapid influenza testing. This study will not assess the accuracy of the POCT analyzer but will use the machine for its approved purpose.

The swab will be inoculated in a test kit and tested on the cobas Liat analyzer as soon as possible after being taken. The results will be available to the clinician in less than 20 minutes.

Antimicrobial prescribing and other study outcomes for those who have been swabbed will be obtained by linking information from the cobas Liat analyzer with data from the patient’s computerized medical record in primary care. We will demonstrate the feasibility of reporting antimicrobial stewardship and severe outcomes postinfection. Severe outcomes postinfection such as hospitalization and mortality will be obtained by linking the patient’s primary care computerized medical record to secondary care records at the national level including hospitalization and mortality data. A recent study used a linked cohort to study severe outcomes from COVID-19 infection [25].

### Virtual Recruitment of Eligible Patients and Home Swabbing of Recruited Patients

We envisage that the majority of eligible patients will be seen face-to-face for this study. Where the eligible patient is not able to attend the practice in person, they will be told about the study remotely, and verbal consent will be taken.

A home swabbing kit will be sent to consented patients who are not able to attend the practice in person. This will include a nasal swab and instructions on how to take a self-test. Further details of our patients self-swabbing at home service have been previously published [26]. Once the nasal swab has been taken, the patient will be asked to place the swab in the included transport container with the manufacturer-approved universal transport media or viral transport media and inform the study practice staff who will arrange collection of the swab sample within 4 hours of being taken for immediate POCT.

### Clinical Workflow Integration

Data regarding the utility of the influenza POCT in primary care and the issues and barriers to implementation of influenza POCT in primary care workflows will be collected by ethnographic observation of study practices and by a semistructured survey of clinicians and practice staff at the participating practices. Information will be collected about the following domains previously found to be important to implementation of POCT sampling [27]: usability of the POCT platform, clinical pathways and training, result reporting, clinical governance, costs, monitoring of effectiveness.

The ethnographic observations, semistructured survey, and reported POCT results will be used to assess which practices were more successful at integrating POCTs into their practice processes by comparing business process models of the practices. Business process models are graphical representations of business-oriented processes within an organization. This is helpful to model collaborations and business transactions within health systems. Business processes are typically modeled using Business Process Modeling Notation (BPMN). BPMN can be used to depict the end-to-end flow of a business process. The notation has been specifically designed to coordinate the sequence of processes and the messages that flow between different process participants in a related set of business activities [28,29].

